#### Beck's Depression Inventory (BDI).

This questionnaire will be conducted on the 1st treatment visit, before the treatment, 1 week after the last treatment, and at the 6-month follow-up. It is composed of 21 questions, and a value from 0 to 3 points is assigned to each answer. A higher score means a more severe depressive state. Clinical depressive disorder is diagnosed when the total score is 17 or above. In this case, the investigators will invite the participant to visit a psychological clinic.

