**Timetable**

| Time point                                                                                  | Study period |                      |                  |        |        |        |                 |         |         |
|---------------------------------------------------------------------------------------------|--------------|----------------------|------------------|--------|--------|--------|-----------------|---------|---------|
|                                                                                             | Enrollment   | Allocation           | Active Treatment |        |        |        | post-allocation |         |         |
|                                                                                             | Week -1      | Week 0
(Baseline) | Week 1           | Week 2 | Week 3 | Week 4 | Week 5          | Month 3 | Month 6 |
| Visit window                                                                         |              |                      | ±3               | ±3     | ±3     | ±3     | ±3              | ±7      | ±7      |
| Eligibility screening                                                                       | ○            |                      |                  |        |        |        |                 |         |         |
| Written Informed consent                                                                    | ○            |                      |                  |        |        |        |                 |         |         |
| Vital signs                                                                                 | ○            |                      | ○                |        |        |        | ○               |         |         |
| Sociodemographic characteristics,
medical history
(e.g. TMJ pain, medication history) | ○            |                      |                  |        |        |        |                 |         |         |
| RDC/TMD test & analysis                                                                     | ○            |                      |                  |        |        |        |                 |         |         |
| Randomized allocation                                                                       |              | ○                    |                  |        |        |        |                 |         |         |

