### **3.5. Sample size calculation**

Calculation of the number of clinical study subjects: As this study is an investigator-initiated clinical trial, the sample size was determined by referencing existing similar studies and clinical experience..

- 1) Level of significance,  $\alpha=0.05$ (two-tailed test)
- 2) Type II error ( $\beta$ ) is set at 0.2, making the power of the test 80%.
- 3) There is no existing study comparing Korean Chuna therapy and usual care for TMJ-related conditions in Korea. Therefore, based on clinical experience and manual therapy studies in China 1-3), the effect size for comparing the mean differences in pain VAS between the two groups is assumed to be at least medium (effect size = 0.7).
- 4) G\*Power 3.1.7 is used to calculate the sample size.

Assuming an effect size of 0.7, 34 subjects per group (a total of 68 subjects) are required. However, since the main analysis will be performed using ANCOVA, adjusting for baseline outcome values, and assuming a correlation value of 0.3 between baseline and the primary endpoint, the sample size is calculated as  $(1 - 0.3 * 0.3) * 68$ , resulting in 62 subjects. Considering a 30% dropout rate during the study, a total of 80 subjects will be recruited, with 40 subjects per group.

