#### 5.2.2. Allocation concealment and blinding

After providing patients with a thorough explanation of the clinical study, those who meet the inclusion and exclusion criteria and sign the written consent form will be assigned to groups using opaque, sealed envelopes. Since it is not feasible to blind the practitioners and participants in this study, only the assessors will be blinded. Assessor, who do not participate in the procedures and are blinded to group assignments, will conduct assessments in a separate area after the procedures are completed. These evaluations will be performed by clinical research coordinator or residents.

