## 6. Outcomes

### 6.1. Primary outcomes

#### Visual Analogue Scale (VAS) for TMJ pain

VAS will be evaluated on the 1st, 3rd, 5th, and 7th treatment visits (week 1–4) and 5 weeks, 3 months, and 6 months after allocation. The average TMJ pain for the past week will be investigated. The primary endpoint is VAS at 5 weeks after allocation (a week after the last treatment). The far left end of a 100 mm scale line means “no pain” and the far right end means “the worst pain imaginable.” It is the most frequently used way to measure the pain severity. A participant puts a mark on the line, which approximates his/her own pain for the past week. If a participant complains of different pain levels on each TMJ, the more severe side will be recorded.

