#### Jaw Functional Limitation Scale (JFLS).

Participants will be asked to complete this questionnaire on the 1st treatment visit, prior to the treatment, and a week after the last treatment. The functions of biting, moving, speaking, and emotional expression will be investigated through 20 items. Each item can be rated in the answer from 0 (no limitations) to 10 (maximum limitation).

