#### Short Form-12 Health Survey (SF-12), version 2.

SF-12 will be conducted on the 1st treatment visit, prior to the treatment, a week after the last treatment, and at the 3-month and 6-month follow-ups. It contains 12 items about health-related quality of life. A higher total score reflects a better quality of life.

5-Level EuroQol-5 Dimension (EQ-5D-5 L) and EuroQol Visual Analogue Scale (EQ-VAS).

EQ-5D-5 L and EQ-VAS will be conducted on the 1st treatment visit, just before the treatment, a week after the last treatment, and at the 3-month and 6-month follow-ups. The EQ-5D-5 L evaluates health state, and the total score is indirectly calculated through a specifically developed equation. It is composed of five items (mobility, self-care, usual activities, pain, and anxiety/ depression). EQ-VAS uses a 100 mm line, which ranges from the worst health condition on the left end to the best health condition on the right end. Participants will be asked to mark the point corresponding to one's own health condition on that day.

Cost data investigation

Cost data include medical consumption, non-medical consumption and productivity loss cost of societal perspective. A questionnaire will be developed to evaluate consumption profiles, such as formal/informal medical consumption, non-medical consumption, and time consumption. While formal medical consumption refers to medical interventions and drugs, informal medical consumption refers to health food, medical instruments, etc. Non-medical consumption includes the cost of transportation, time consumption, and nursing. The Work Productivity and Activity Impairment questionnaire (WAPI) will be used for the cost of productivity impairment [24]. Medical consumption and non-medical consumption will be investigated with questionnaires which contains the cost data and the received treatment of participants and the cost data of Korean National Health Insurance will also be analyzed to calculate consumptions.

Credibility and expectancy questionnaire

The 9-point Likert scale for Credibility and Expectancy This scale is used to assess the participants' expectancy of the trial. On the 1st treatment visit, before the treatment, they will be asked how much the symptom would be reduced by the CMT and UC (1=not at all, 5=somewhat, and 9=very much).

Adverse events

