#### **6.3.2 General principles of analysis**

- This study analyzes the results of pain intensity scale, functional scale, quality of life, and cost data for patients who meet the inclusion criteria in a randomized controlled trial.
- The primary analysis will use the ITT (Intention-to-Treat) approach, evaluating all subjects who received at least one treatment. Additionally, the PP (Per-Protocol) analysis will be conducted alongside, evaluating only those subjects who completed the clinical study without dropping out. Missing data will be handled primarily through Multiple Imputation, and LOCF (Last Observation Carried Forward) will be used for sensitivity analysis.
- The socio-demographic characteristics and treatment expectancy of the study subjects will be evaluated by group. Continuous variables will be expressed as mean (standard deviation) or median (interquartile range) and compared between the two groups using Student's t-test. Categorical variables will be expressed as frequency (%) and analyzed using the chi-square test or Fisher's exact test.
- The efficacy evaluation variables of this clinical study are the differences in the changes of continuous outcomes (VAS, NRS, MMO, K-BDI-2, JFLS, SF-12, EQ-5D-5L, EQ-VAS) between the two groups from baseline to each time point. ANCOVA (Analysis of Covariance) will be performed with the baseline values of each variable and the covariate factors that show statistical differences between the

treatment groups at baseline as covariates, and the group as a fixed factor. RM ANOVA (Repeated Measures ANOVA) will be conducted to test the differences in trends at each visit.

- To compare the total amount of differences in each outcome within the period (evaluation time point after treatment completion (5 weeks)) and the entire study period (6 months), the areas under the curve (AUC) at each time point after randomization will be calculated and compared using Student's t-test.

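### The only baseline K-BDI-2, and most other self-reported baselines, are taken after allocation from participants who are not blinded; taking them before allocation would cost little

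*Protocol*

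**What the plan says.** The timetable places "Randomized allocation" in the Week 0 (Baseline) column. The K-BDI-2 row is marked at Week 1, Week 5 and Month 6 only. Section 6.2 agrees: "This questionnaire will be conducted on the 1st treatment visit, before the treatment, 1 week after the last treatment, and at the 6-month follow-up".

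Other self-reported outcomes follow the same pattern:

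- VAS, the primary outcome (section 6.1): "VAS will be evaluated on the 1st, 3rd, 5th, and 7th treatment visits", with no screening mark in the timetable.
- JFLS (section 6.2): "Participants will be asked to complete this questionnaire on the 1st treatment visit, prior to the treatment".
- SF-12 (section 6.2): "SF-12 will be conducted on the 1st treatment visit, prior to the treatment".
- EQ-5D-5L and EQ-VAS (section 6.2): first taken just before treatment at the same visit. Section 5.1 also starts the quality-of-life measures at visit 2.

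On blinding, section 5.2.2 states: "Since it is not feasible to blind the practitioners and participants in this study, only the assessors will be blinded". On analysis, section 6.3.2 states: "ANCOVA (Analysis of Covariance) will be performed with the baseline values of each variable", and K-BDI-2 is in its list of continuous outcomes.

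**The concern.** Adjusting for a covariate in a randomised comparison is safe when assignment cannot have influenced the covariate. A questionnaire completed after allocation by an unblinded participant does not carry that guarantee. Someone pleased or disappointed with their arm may rate mood, pain or function differently before any treatment is given. ANCOVA would treat the resulting arm difference as a true baseline imbalance and adjust the Week 5 comparison for it.

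The baseline is also used elsewhere in section 6.3.2. It sets the threshold for the analyses of pain falling below half of baseline, and differences between arms at baseline decide which further covariates enter the model.

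The protocol fixes when the forms are completed, and no later analysis plan can recover a pre-allocation score that was never collected.

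**Working it through.** **Order of events.** Section 5.1 has screening, then random assignment, then treatment. The timetable footnote puts visit 2, the first Week 1 visit, on the day of screening or within 3 days.

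| Self-reported outcome in the ANCOVA list | First reading in the timetable | Pre-allocation reading there? |
|---|---|---|
| VAS (primary) | Week 1 | No |
| NRS | Screening | Yes |
| K-BDI-2 | Week 1 | No |
| JFLS | Week 1 | No |
| SF-12 | Week 1 | No |
| EQ-5D-5L | Week 1 | No, although section 5.3.2 mentions a pre-study measurement |
| EQ-VAS | Week 1 | No |

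Six of the seven have no scheduled reading before allocation. Mouth opening is also in the ANCOVA list but is measured rather than self-reported.

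**Size, as a conditional illustration.** The documents give no figure for how far knowledge of the arm shifts a baseline report, so the shift below is an assumption.

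Inputs:

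- Correlation r = 0.3. Section 3.5 gives it for the primary endpoint ("assuming a correlation value of 0.3 between baseline and the primary endpoint"); using it for the other outcomes is an assumption. It reproduces the plan's reduced total: (1 − 0.3²) × 68 = 61.88, so 62, or 31 per arm.
- n = 40 per arm as recruited, and 31 per arm for the 62 that section 3.5 requires.
- Planned effect 0.7 SD on VAS and two-sided alpha 0.05 (section 3.5).
- Assumed between-arm shift s in reported baseline of 0.1, 0.2 or 0.3 SD, with equal SDs at baseline and follow-up, no true effect, and no shift in the follow-up score.

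Formulas:

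- Movement of the adjusted difference = r × s.
- Standard error = √[(2/n)(1 − r²)]. For n = 40: √(0.05 × 0.91) = 0.213 SD. For n = 31: √(0.0645 × 0.91) = 0.242 SD.
- Type I error from the noncentral t with 2n − 3 degrees of freedom and noncentrality (r × s)/SE.

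| s (assumed) | r × s at r = 0.3 | In SEs, n = 40 | Type I error, n = 40 | Type I error, n = 31 | Share of 0.7 (VAS) |
|---|---|---|---|---|---|
| 0.1 SD | 0.03 SD | 0.14 | 0.052 | 0.052 | 4% |
| 0.2 SD | 0.06 SD | 0.28 | 0.059 | 0.057 | 9% |
| 0.3 SD | 0.09 SD | 0.42 | 0.070 | 0.065 | 13% |

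A simulation of 8,000 runs at 40 per arm moved the estimate by 0.029, 0.061 and 0.092 SD, with type I error 0.052, 0.058 and 0.069. This agrees with the formulas.

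The result depends on r. At an assumed r = 0.6 the movement doubles to 0.06, 0.12 and 0.18 SD. The standard error at 40 per arm is √(0.05 × 0.64) = 0.179 SD, and the type I error is 0.063, 0.102 and 0.169.

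**The case against.** The harm needs participants to know their arm when they complete the form, and the protocol does not say when they are told. Week 0 seems to have no visit of its own: with visit 1 as screening and visit 2 as the first treatment, allocation falls at one or the other. A site could open the envelope after the visit 2 questionnaires. This stands as a limit. However, the timetable as written puts allocation before these readings and nothing requires the safer order, which is a reason to write it down.

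Section 5.3.2 lists a quality-of-life measurement before participation, using tools such as the EQ-5D-5L, and this could be read to include SF-12 and EQ-VAS. That weakens the point for those three, although the timetable and sections 5.1 and 6.2 place their first reading at visit 2. It does not touch K-BDI-2, JFLS or VAS. For VAS, section 6.1 does not even say that the first reading precedes treatment.

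The illustration shifts only the baseline. If the same shift s persisted to Week 5, the bias would be s − r × s = 0.7s with the planned baseline at r = 0.3, against s with a pre-allocation one. The direction of any shift is also unknown, and unblinded self-report at follow-up enters the estimate at full weight whichever baseline is used. All of this is correct. The change closes one route and does not promise a lower total bias. It is still no reason to prefer a covariate that assignment may have affected, because any cancellation would be accidental and of unknown size.

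**Conclusion.** The point holds as a cheap improvement, not as a demonstrated bias. The protocol schedules the sole K-BDI-2 baseline after allocation in unblinded participants and uses it as the ANCOVA covariate; five other self-reported outcomes, including the primary VAS, share that schedule. At the plan's own correlation any effect is probably small, at most 0.42 standard errors over the range of shifts considered. It would be larger with a stronger baseline correlation. These sizes rest on assumed shifts confined to baseline, equal SDs, and participants knowing their arm when they answer. The K-BDI-2, JFLS, SF-12, EQ-5D-5L and EQ-VAS are stated to precede the first treatment, so for them the only route is knowledge of the allocation.

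**What to change.** In the timetable and sections 6.1 and 6.2, have participants complete the baseline K-BDI-2 at the screening visit after consent, or at the latest before the allocation is opened, and name that score as the ANCOVA baseline. Move the first VAS, JFLS, SF-12, EQ-5D-5L and EQ-VAS with it. Keep all later readings, and leave the eligibility and withdrawal criteria unchanged.

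The cost is a timetable and wording amendment. It needs no new visit or instrument and leaves the sample size at 80. Screening is at most 3 days before visit 2, and NRS is already collected there. With completion at screening, some screen failures will fill in the forms. Referrals for K-BDI-2 scores of 17 or above will arise at screening, including for people who are then not enrolled, and the baseline may be up to 3 days older. Completing the forms after eligibility is confirmed but before the allocation is opened avoids most of this.

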#### Jaw Functional Limitation Scale (JFLS).

Participants will be asked to complete this questionnaire on the 1st treatment visit, prior to the treatment, and a week after the last treatment. The functions of biting, moving, speaking, and emotional expression will be investigated through 20 items. Each item can be rated in the answer from 0 (no limitations) to 10 (maximum limitation).

#### Patient Global Impression of Change (PGIC).

The PGIC questionnaire will be administered a week after the last treatment, and at the 3-month and 6-month follow-ups. Participants will subjectively evaluate the improvement of their health state with a 7- point Likert scale, ranging from 1 (very much improved) to 7 (very much worse).

#### Short Form-12 Health Survey (SF-12), version 2.

SF-12 will be conducted on the 1st treatment visit, prior to the treatment, a week after the last treatment, and at the 3-month and 6-month follow-ups. It contains 12 items about health-related quality of life. A higher total score reflects a better quality of life.

5-Level EuroQol-5 Dimension (EQ-5D-5 L) and EuroQol Visual Analogue Scale (EQ-VAS).

EQ-5D-5 L and EQ-VAS will be conducted on the 1st treatment visit, just before the treatment, a week after the last treatment, and at the 3-month and 6-month follow-ups. The EQ-5D-5 L evaluates health state, and the total score is indirectly calculated through a specifically developed equation. It is composed of five items (mobility, self-care, usual activities, pain, and anxiety/ depression). EQ-VAS uses a 100 mm line, which ranges from the worst health condition on the left end to the best health condition on the right end. Participants will be asked to mark the point corresponding to one's own health condition on that day.

Cost data investigation

Cost data include medical consumption, non-medical consumption and productivity loss cost of societal perspective. A questionnaire will be developed to evaluate consumption profiles, such as formal/informal medical consumption, non-medical consumption, and time consumption. While formal medical consumption refers to medical interventions and drugs, informal medical consumption refers to health food, medical instruments, etc. Non-medical consumption includes the cost of transportation, time consumption, and nursing. The Work Productivity and Activity Impairment questionnaire (WAPI) will be used for the cost of productivity impairment [24]. Medical consumption and non-medical consumption will be investigated with questionnaires which contains the cost data and the received treatment of participants and the cost data of Korean National Health Insurance will also be analyzed to calculate consumptions.

Credibility and expectancy questionnaire

The 9-point Likert scale for Credibility and Expectancy This scale is used to assess the participants' expectancy of the trial. On the 1st treatment visit, before the treatment, they will be asked how much the symptom would be reduced by the CMT and UC (1=not at all, 5=somewhat, and 9=very much).

Adverse events

Adverse events are undesirable and unintended signs (e.g., abnormal laboratory findings), symptoms, or diseases that occur after procedures during the clinical study, and they do not necessarily have to be causally related to the procedure. The analysis primarily includes adverse events suspected by the researcher to be related to the treatment, abnormal laboratory values, and the frequency of serious adverse events. Collected safety data are appropriately summarized, with all serious adverse events described narratively. Adverse events are collected through patient symptom reports and researcher observations and are identified by the frequency of adverse events between groups. The researcher will evaluate the causal relationship between each treatment method and the observed adverse events using a six-step scale (1 = definitely related, 2 = probably related, 3 = possibly related, 4 = probably not related, 5 = definitely not related, and 6 = unknown). All side effects will also be classified into three categories according to Spilker's classification method: Mild (1) - not requiring treatment and not significantly interfering with the subject's normal life (function); Moderate (2) - significantly interfering with the subject's normal life (function) and may require treatment, with recovery after treatment; Severe (3) - requiring intensive treatment due to severe adverse events and leaving sequelae.

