#### 7.4. Assessment Methods

All anticipated phenomena (symptoms and signs, onset date, duration, etc.) resulting from adverse events during Chuna therapy must be recorded in the adverse event report form. Unrecorded events are classified as subjective symptoms. Adverse events are documented in separate case report forms to prevent exposure of patient assignment groups. The severity of symptoms is evaluated in stages based on the evaluation criteria. Causality with the procedure is assessed using the WHO-UMC causality scale, which classifies the relationship into six categories. The severity of subjective and objective symptoms is evaluated using Spilker's three-tier classification.

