##### *Spilker's Three-Tier Classification*

- Mild (1): Does not require treatment and does not significantly impair the subject's normal life (function).
- Moderate (2): Significantly impairs the subject's normal life (function), may require treatment, and recovers after treatment.
- Severe (3): Requires intensive treatment due to severe adverse reactions, and may result in sequelae.

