### **7.5. Interpretation Method**

All adverse events reported during the study period are tabulated, and the incidence rate is calculated. The proportion of patients experiencing adverse events in each group is compared using Chi-square test or Fisher's Exact test.

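### Sections 6.2 and 7.5 give two different main safety analyses (events suspected to be related versus all events), and Sections 6.2 and 7.4 define severe differently

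*Protocol*

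**What the plan says.** Four parts of the protocol bear on this.

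- **Section 6.2, Adverse events.** Adverse events are defined without a causal requirement: "they do not necessarily have to be causally related to the procedure". The analysis set is then narrowed: "The analysis primarily includes adverse events suspected by the researcher to be related to the treatment". Laboratory abnormalities and counts of serious events complete that set. The same paragraph says that events "are identified by the frequency of adverse events between groups". The researcher rates the causal link with each treatment on a six-step scale. Severe is described as "requiring intensive treatment due to severe adverse events and leaving sequelae".
- **Section 7.4.** Causality again has six categories. Severe is described as "Requires intensive treatment due to severe adverse reactions, and may result in sequelae". The recording sentence covers anticipated phenomena "resulting from adverse events during Chuna therapy must be recorded in the adverse event report form", and the next sentence classes events that were not recorded as subjective symptoms.
- **Section 7.5.** "All adverse events reported during the study period are tabulated, and the incidence rate is calculated". The proportion of patients with events in each group is compared by chi-square or Fisher's exact test.
- **Section 5.2.2.** Practitioners and participants are not blinded; only assessors are. Section 7.2 gives the monitoring for events to practitioners.

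Section 6.3, and the statistical methods repeated at the end of the document, contain no rule for adverse events.

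**The concern.** Sections 6.2 and 7.5 put different events in the numerator of the main safety result, and nothing in the document ranks one above the other. This is not detail left for a statistical analysis plan, because the protocol states both rules.

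The choice matters because relatedness is a judgement. In a trial where the people giving treatment know the arm, a researcher may more readily attribute a sore jaw or neck to manual therapy than to heat or TENS, or may be slower to do so. If related events become the headline, that habit enters the group contrast. Counting all events keeps it out.

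The second problem is grading. With two texts for severe, sites can grade the same event differently, and the severity table then depends on which page was open.

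**Working it through.** **1. Analysis set, side by side**

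| | Section 6.2 | Section 7.5 |
|---|---|---|
| Events counted | Primarily those suspected to be related, plus laboratory abnormalities and serious events | All reported events |
| Causality assessment enters | Yes | No |
| Group comparison | Event frequency between groups, no test named | Proportion of patients with events, chi-square or Fisher |

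The analysis-set conflict is between 6.2 and 7.5. Section 7.4 does not contradict 6.2 on causality: both use six categories with corresponding labels.

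**2. Who assesses causality**

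Section 6.2 says only that it is the researcher. Three statements point to knowledge of the arm: only assessors are blinded (5.2.2), practitioners monitor for events (7.2), and the link is rated for each treatment (6.2). One points the other way: 7.4 keeps adverse event forms separate so that assignment is not exposed. Attribution made knowing the arm is therefore probable but not stated.

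**3. What differential attribution could do**

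The protocol gives no adverse event rate and no attribution rate, so there is no figure of its own to reproduce.

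- From the protocol: 40 patients per arm (Section 3.5), two tests (7.5), significance level 0.05 (6.3.2).
- Assumed: a true event rate t, equal in both arms, from 10% to 40%; and the share s of patients with an event whose event is called related, in each arm.

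Recorded rate in an arm = t × s. For example, 0.30 × 0.80 = 24% and 0.30 × 0.40 = 12%. In 40 patients per arm that is 9.6 against 4.8 expected patients, with no true difference.

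The false-positive rate is the sum, over all pairs of counts (a, b) from 0 to 40, of Bin(a; 40, t·s₁) × Bin(b; 40, t·s₂), taken where the two-sided p-value is at most 0.05. The chi-square test is uncorrected.

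| True rate, both arms | Share called related | Recorded rates | Fisher | Chi-square |
|---|---|---|---|---|
| 10% | 80% v 40% | 8% v 4% | 2.4% | 11.6% |
| 20% | 80% v 60% | 16% v 12% | 4.3% | 8.5% |
| 20% | 80% v 40% | 16% v 8% | 11.3% | 20.8% |
| 30% | 80% v 80% | 24% v 24% | 2.9% | 5.0% |
| 30% | 80% v 60% | 24% v 18% | 6.4% | 10.1% |
| 30% | 80% v 40% | 24% v 12% | 20.9% | 29.2% |
| 40% | 80% v 40% | 32% v 16% | 30.5% | 39.2% |
| 30% | all events counted | 30% v 30% | 2.8% | 4.8% |

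With all events counted and t from 10% to 40%, the rate is 1.7% to 3.0% (Fisher) and 4.8% to 5.9% (chi-square). With equal attribution of 80% it is 1.2% to 2.9% and 4.8% to 5.8%. The inflation comes only from a difference in attribution between arms.

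**4. Severity, side by side**

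Take an event that disrupts normal life, needs intensive treatment and then resolves fully. Under 6.2 it fails the wording for severe, because there are no sequelae. It does meet the wording for moderate, which covers events that may need treatment and recover after it. Under 7.4 it meets the wording for severe, because sequelae are only possible. The same event can be grade 2 in one section and grade 3 in the other.

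**5. Recording**

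The 7.4 sentence names only Chuna therapy. Section 7.6 requires all symptoms seen after a procedure to be recorded, the timetable collects adverse events at every treatment visit and at follow-up, and 7.4 itself lists actions taken in both groups. The 7.4 sentence is narrower than the rest of the protocol. The sentence on unrecorded events cannot be applied, since an event that is not recorded cannot be classified.

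**The case against.** The strongest reply is that the only between-group safety test in the protocol is the one in 7.5. It counts patients with any event, and neither causality nor severity enters it. The word for primarily in 6.2 is not exclusive, and the same paragraph speaks of event frequency between groups. No section prescribes a test of related events. All of this stands. It means that the false-positive rates above describe what would happen if the 6.2 set were put through the 7.5 tests, not what the protocol plans to do. It does not remove the conflict, because 6.2 still names a different main analysis set.

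Four stronger readings are tempting, and the documents do not support them:

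- *Causality is assessed by unblinded researchers.* The blinding of that role is not stated. It is an inference, and the separate forms in 7.4 count somewhat against it.
- *Under 6.2 an event that needs intensive treatment and resolves has no grade.* It can be placed in moderate.
- *Events in the usual care arm need not be recorded.* Section 7.6, the timetable and the both-group action list in 7.4 cover them.
- *The severity mismatch biases the group comparison.* It affects severity tables only.

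It is also fair to say that the attribution percentages are invented for illustration and presuppose the difference whose effect they show.

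**Conclusion.** The plan is wrong as written on two specific points: it states two main safety analysis sets without ranking them, and it gives two definitions of severe. The first could distort the safety headline, but only if 6.2 governs and attribution differs by arm. The probable lack of blinding of the person who attributes makes the second condition plausible without proving it.

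Under assumed attribution of 80% versus 40%, the false-positive rate for a related-only comparison runs from 2.4% to 30.5% by Fisher's test and from 11.6% to 39.2% by chi-square as the true rate goes from 10% to 40%. With equal attribution there is no inflation. These are illustrations, not estimates for this trial. The severity mismatch changes grading, not the 7.5 test. The recording sentences in 7.4 are loose drafting. The matter concerns a secondary safety outcome and should be corrected, but it does not touch the primary efficacy result.

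**What to change.** 1. Change the analysis sentence in 6.2 so that all adverse events by group, regardless of causality, are the main safety comparison as in 7.5. Report events suspected to be related as a supplementary descriptive table.
2. Reconcile the two definitions of severe to one text and use it in both 6.2 and 7.4. The study team must decide which text applies.
3. Align the recording sentence in 7.4 with 7.6, so that it covers every event in either group, and remove or rewrite the sentence on unrecorded events.

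The cost is an amendment to the protocol wording and to any matching case report form guidance. No new data, visits or patients are needed.
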